## **General and specific objectives**

### General objective:

The main purpose of this project is to develop and validate a work-model for Primary Care for identifying patients with OSA, based on clinical variables and an ambulatory monitoring study.

### Specific objectives:

- To establish the validity of an ambulatory monitoring device for identifying patients with OSA and to compare it with the RP / PSG performed at the Sleep Unit.
- To create a screening model for the detection of OSA.
- To analyze the validity of the treatment decision (CPAP vs. no CPAP) made by the PCPs, by using the ambulatory monitoring study, in relation to the decision made by the specialist Sleep Unit.
- To make an analysis of costs, including the cost-effectiveness of an outpatient strategy vs. a strategy including assessment at the Sleep Unit.

## **Methods**

Study Design: Prospective and multicenter study.

Study population:

Patients visited in Primary Care centers will be consecutively included until the necessary sample size is reached. They will be selected according to a randomization schedule to avoid bias in the inclusion.

Inclusion Criteria:

- Patients between 18 and 75 years of age.

Exclusion Criteria:

- Cognitive impairment or psycho-physical deterioration that impede the performance of an ambulatory monitoring study.
- Worsened or unstable cardio-vascular or cerebro-vascular disease.
- Chronic insomnia (<5h sleep / day).
- Previous diagnosis of OSA.
- Relevant respiratory comorbidity that could interfere with arterial saturation measurements, such as moderate to severe chronic obstructive pulmonary disease ( $FEV1/FVC < 0,70$  y  $FEV1 < 50\%$  ref.v.).
- Neuromuscular disease.
- Refusal to participate in the study.

### Field of study:

Three Sleep Units at three University Hospitals in Barcelona:

- .- Hospital de la Santa Creu i Sant Pau (coordinator)
- .- Hospital de la Vall d'Hebron
- .- Hospital del Mar
- .- Hospital Dos de Maig

Six Primary Care centers in the reference area of these three hospitals.

### Outcome Measures

- Primary outcome: apnea-hypopnea index (AHI) obtained in Sleep Unit by PSG/RP study.
- Secondary outcomes:

Anthropometric and socio-demographic data: age, sex, weight, height, body mass index (BMI) and waist circumference.

Evaluation of medical history and cardiovascular risk factors: hypertension, diabetes, dyslipidemia, smoking, alcoholism, metabolic syndrome, heart disease (ischemic heart disease, arrhythmia, heart failure), cerebro-vascular disease (transient ischemic attack, ischemic or hemorrhagic) and peripheral vascular disease. Drug treatment.

Medical records focussed on Respiratory Sleep Disorders: specific clinical questionnaire on symptoms suggestive of OSA. Berlin-questionnaire in Spanish version. (Chest 2003;124:1406-1414).

Lung function tests: spirometry according to SEPAR recommendations. (Arch Bronconeumol 2013; 49: 388-401).

Self-perceived sleepiness analyzed by Epworth scale (MW Johns, Sleep 1991; 14: 540; validation in Castilian: Med Clin Ferrer M 1999.113: 250-255.).

Respiratory Polygraphy (RP) / Conventional Polysomnography (PSG):

Apnea-hypopnea index (IAH), obstructive apnea index, hypopnea index, central apnea index, mixed apnea index, sleep efficiency (total sleep time/recording time), percentage of time of phases NREM1, NREM2, NREM3 and REM, initial saturation, mean saturation (SO2), minimum saturation and cumulative time percentage with saturation lower than 90% (CT90%).

Ambulatory monitoring study (AMS): AHI, mean saturation, 4% desaturation index (ID4%), 3% desaturation index (ID3%) and CT90%.

### Sample size

The sample size has been calculated considering a minimum prevalence of 25% of OSA in the population attending Primary Care Medicine. Assuming 15% of losses to follow-up, an error of 5% and a power of 90%, a total sample of 198 patients was estimated as necessary to achieve a sensitivity of 90%.

According to the methodology proposed by Chai-Coetzer et al. (Thorax 2011; 66: 213-219), the screening study will be carried out taking into account clinical probability based on the Berlin Questionnaire (Netzer NC. Chest 2003; 124:1406-14). The study will be carried out in all patients with a high probability of OSA but in only 1 of 3 patients with a low probability. Therefore, a minimum of 396 valid questionnaires must be completed.

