#### Data management and analysis

The main objective of this study is to obtain a sufficiently accurate calculation of the area under the curve (AUC) of the Receiver Operating Characteristics (ROC) curve. The expected sensitivity value is high, close to 90%. With this number of cases the accuracy of the AUC will not be less than 10%. In all cases, the interval confidence of calculated rates is assumed to be 95%.

A descriptive analysis will be performed using means, medians, confidence intervals, interquartile ranges for quantitative variables and table of frequencies for qualitative variables. In qualitative variables, the Chi-square test or Fisher exact test will be used for bivariate analysis. In the case of quantitative variables, the T-test or Mann-Whitney U test will be performed according to normal distribution.

Finally, logistic regression will be used to find the best clinical prediction model. Variables showing clinical significance in the bivariate analysis and those considered clinically relevant will be included. A goodness-of-fit test (Hosmer Lemeshow test) will be performed to validate the resulting model. The AUC of the ROC will be used to calibrate the model.

In all cases, the significance level will be, as usual, 5% ( $\alpha = 0.05$ ), bilateral approach.

We will use IBM-SPSS (V. 21.0) software to perform the analysis.

In the analysis of costs we will consider the direct costs of all the tests (ambulatory monitoring study, polygraphy or polysomnography), staffing costs, the amortization of the devices, the transfer of the patients and the number of visits. We will also take into account the false-positive and negative diagnosis (*Pietzoch JB et al. An integrated Health-Economic Analysis of Diagnostic and Therapeutic strategies in the treatment of moderate to severe obstructive sleep apnea. Sleep 2011;34: 695-709*).

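### The sample size claims 90% power to reach 90% sensitivity but gives no null value, and power, main objective and primary outcome name three different targets

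*Protocol*

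**What the plan says.** Protocol, Sample size: the calculation starts from "a minimum prevalence of 25% of OSA in the population attending Primary Care Medicine". Its other inputs are a 15% allowance for dropout, a 5% error rate and 90% power. The conclusion drawn is "a total sample of 198 patients was estimated as necessary to achieve a sensitivity of 90" per cent. The same section then has the screening study done in every patient with a high Berlin probability of OSA but in only 1 of 3 with a low probability, which requires at least 396 valid questionnaires.

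Protocol, Data management and analysis: the aim is given as "The main objective of this study is to obtain a sufficiently accurate calculation of the area under the curve (AUC"). The curve meant is the ROC curve. Sensitivity is anticipated to lie near 90%. On precision, the section states "With this number of cases the accuracy of the AUC will not be less than 10" per cent. Rates are to be reported with 95% confidence intervals. On testing, it states "In all cases, the significance level will be, as usual, 5" per cent, two-sided. The methods listed are bivariate tests, logistic regression, the Hosmer-Lemeshow test and the AUC.

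Protocol, Outcome Measures: "Primary outcome: apnea-hypopnea index (AHI) obtained in Sleep Unit by PSG/RP study".

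**The concern.** A number of patients cannot bring about a sensitivity. It can give a stated chance of showing that sensitivity exceeds some lower value, or a stated width of interval around the estimate. The sentence quotes a power but omits the lower value, so 198 cannot be derived from the inputs printed beside it. A reader will probably take it as 90% power to confirm 90% sensitivity.

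The other sections do not settle the matter. The analysis section aims at an AUC, and the outcome section names the Sleep Unit AHI. That AHI is the yardstick for the screening model, not a measure of how well the model performs. The Hypothesis section expects great diagnostic reliability but gives no value below which that would be judged not met. What is at stake is whether a result can be called a success or a failure by a rule fixed in advance, and whether 198 is presented for what it can deliver.

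**Working it through.** **Inputs.** From Sample size: prevalence 0.25, losses 0.15, error 5%, power 90%, sensitivity 0.90. From Data management and analysis: two-sided. Not stated anywhere: the null sensitivity p0. I assume a range of values for it.

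**Reproducing 198.** One-sample test of a proportion among patients with OSA:

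n = [1.96·√(p0(1−p0)) + 1.2816·√(0.9·0.1)]² / (0.9−p0)²

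With p0 = 0.70: n = 41.1, so 42 cases. 42/0.25 = 168 evaluable. 168/0.85 = 197.6, so 198 enrolled.

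| Assumed p0 | Cases | Enrolled |
|---|---|---|
| 0.60 | 21 | 99 |
| 0.65 | 28 | 132 |
| 0.70 | 42 | 198 |
| 0.75 | 68 | 320 |
| 0.80 | 137 | 645 |

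The missing input therefore largely determines the size of the study.

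**Other routes to about 198.**
- Null 75% with the variance taken at 90% only: 43 cases, 172 evaluable, 203 enrolled (172/0.85) or 198 (172 × 1.15).
- One-sided 5%, null 73%: 43 cases, 203 or 198.
- A ±9-point Wald interval with no power: 1.96²·0.09/0.09² = 42.7, so 43 cases, 203 or 198.
- AUC 0.85 against 0.70 (Hanley-McNeil): 41 cases, 193.

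**What 42 cases can show if true sensitivity is 90%** (exact binomial, upper-tail error at most 2.5%):

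| Null | Detected cases needed, of 42 | Exact power |
|---|---|---|
| 70% | 36 | 88% |
| 75% | 38 | 59% |
| 80% | 39 | 38% |

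The chance of observing at least 90% (38 or more of 42) is 59%. If 38 of 42 are detected (90.5%), the exact 95% interval is 77% to 97%, about 13 points below the estimate and 7 above. The Wald half-width, 1.96·√(0.09/42) = 9.1 points, understates the lower side.

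**AUC claim.** With 42 cases and 126 non-cases, the Hanley-McNeil 95% half-width is 0.097 at AUC 0.70, 0.086 at 0.80 and 0.065 at 0.90. The claim therefore holds, ignoring the sampling, if it means a half-width of no more than 0.10. As worded, it puts a floor where a ceiling is meant.

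**Effect of the 1-in-3 sampling.** Let H and L be the numbers with high and low probability. H + L = 396 and H + L/3 = 198 give L = 297 and H = 99, so 99 high and 99 low are studied. After 15% losses about 84 of each remain. Let h be the OSA risk in the high group (not stated; assumed 25% to 60%). Holding overall prevalence at 25%, the low-group risk is (1−h)/3.
- Cases studied: 84h + 84(1−h)/3 = 28(1+2h), which is 42 at h = 25% and 62 at h = 60%.
- Effective cases, with weight 1 for high and 3 for low: (Σw)²/Σw² = 84/(3−2h), which is 33.6 at 25%, 40 at 45%, 42 at 50% and 46.7 at 60%.

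So the 42 in the protocol's apparent calculation corresponds to the weighted estimate only when h is about 50%.

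**The case against.** The best defence has four parts.

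**The inferential tool is there.** Calculated rates are to have 95% intervals at a two-sided 5% level, and sensitivity is such a rate. A lower 95% limit serves as a test once a reference value exists. This stands. A reader might infer that sensitivity is never tested, but the documents do not support that: what is missing is the reference value and its criterion, and a formal test may be in a SAP that was not available here.

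**The 70% is back-calculated.** A reader might infer that 198 can only come from a 70% null, and so that the study can only show sensitivity above about 70%. That is too strong. The value is never stated, and other routes reach 198 or come within 3% of it. The 70% is the cleanest match under the stated error, power and sidedness, no more. That several targets fit does not excuse the omission, because the text still does not say which was used.

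**The sampling may do no harm.** A reader might infer that the 1-in-3 scheme costs power. That is not shown. The low end of 34 effective cases needs the Berlin questionnaire to carry no information about OSA. Near 50% risk in the high group the effect is nil, and at 60% it is a gain. What stands is that the calculation does not address the scheme.

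**The primary outcome is a matter of labelling.** The Specific objectives and the Design and Validation section already make RP/PSG the comparator. This is fair, but the label still leaves the screening model without a named primary accuracy measure.

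**Conclusion.** The point holds in this form: the 90% power is quoted without the null that would give it meaning, and the wording credits the design with a property it does not have. On 42 cases and a true sensitivity of 90%, exact power is 88%, 59% and 38% against 70%, 75% and 80%. These figures assume 25% prevalence, 15% losses and simple random sampling. Under the protocol's own sampling scheme the effective number of cases is about 34 to 47, assuming 25% to 60% OSA risk in the high-probability group. The sensitivity, AUC and AHI targets in three sections should be reconciled. None of this shows that 198 is too few. It shows that the text does not say what 198 is enough for.

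**What to change.** 1. Replace the power sentence in one of two ways. Either state the null sensitivity the sponsor actually used, with the matching criterion that the lower 95% limit exceeds it (if it was 70%, about 88% exact power under simple random sampling). Or give a precision statement: about 42 cases, exact 95% interval about 77% to 97% if 90% is observed. The minimum acceptable sensitivity is the sponsor's judgement and should not be taken from the back-calculation.
2. Name one primary accuracy measure of the screening model against the Sleep Unit AHI, and label that AHI the reference standard.
3. Estimate sensitivity and AUC with weights for the 1-in-3 sampling. State power or precision for the weighted estimate as a range over the assumed OSA risk in the high-probability group (effective cases about 34 to 47 for 25% to 60%).
4. Word the AUC claim as a 95% interval half-width of no more than 0.10.

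The cost is rewording, with no extra patients. The stated claim becomes less favourable.

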## Limitations

- Limitations of RP: sleep time is not equivalent to study time and this can underestimate the values. To avoid this, we will take into account the quality of sleep provided by the patient. Thus, this aspect will not significantly limit the main objective: to differentiate patients with severe disease or mild disorders.
- Acceptance rate of participation: In a previous study with similar characteristics, the acceptance rate of participation was 40% of the survey respondents. Considering the large population usually attended at Primary Care centers in the urban area of Barcelona, this is not an expected limitation for reaching sample size. We must take into account that patients accepting their inclusion in the study could be those with greater comorbidity. This could give rise to a bias in the sample.

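### Berlin-low patients are sampled at 1 in 3, but no analysis in the protocol accounts for it, so crude accuracy of Berlin-based rules and the cost inputs would not describe Primary Care

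*Protocol*

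**What the plan says.** The Sample size section of the protocol bases the 198 patients on "a minimum prevalence of 25% of OSA in the population attending Primary Care Medicine", with 15% losses, 5% error, 90% power and a target sensitivity of 90%. It then adds that screening is to be "carried out in all patients with a high probability of OSA but in only 1 of 3 patients with a low probability", so that "a minimum of 396 valid questionnaires must be completed".

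Other sections describe selection differently:

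- Methods, Study population: "Patients visited in Primary Care centers will be consecutively included until the necessary sample size is reached". It adds that a randomization schedule is used to avoid inclusion bias. Berlin-dependent fractions are not mentioned, and it is not said whether that schedule is the 1-in-3 draw.
- Methodology, Design and Validation Time: every patient eligible for inclusion undergoes both evaluations.

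Data management and analysis names the AUC of the ROC curve as the main objective. It expects sensitivity near 90% and lists bivariate tests, logistic regression, the Hosmer-Lemeshow test and a cost analysis that takes account of false-positive and false-negative diagnoses. It mentions no sampling weights, no stratification by Berlin result and no standardisation. The objectives and the Rationale place the model in Primary Care, where it should allow OSA to be ruled out.

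**The concern.** The design has two phases. The Berlin result decides the chance of being studied: 1 for high, 1/3 for low. Berlin is also one of the clinical variables collected under Outcome Measures, so selection acts through a candidate predictor. Berlin-low patients, among whom a rule-out strategy would miss cases, are under-represented threefold relative to Berlin-high patients.

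If the listed analyses are run on the studied patients as they stand, sensitivity and specificity of Berlin, or of any rule built on it, describe an enriched sample. The false-positive and false-negative counts in the cost comparison carry the same case mix. A Hosmer-Lemeshow test on that same sample cannot reveal the problem.

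**Working it through.** **Inputs from the protocol.** Sampling fractions 1 (Berlin-high) and 1/3 (Berlin-low); 396 questionnaires; 198 patients; 25% prevalence in Primary Care; 15% losses; 5% two-sided error; 90% power; sensitivity 90%.

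**Assumptions.** Berlin-high share h (back-solved), OSA prevalence within Berlin strata, and AMS accuracy by stratum.

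**1. Reproducing 396.** 396 × [h + (1 − h)/3] = 198 gives h + (1 − h)/3 = 0.5, so h = 0.25. That is 99 high plus 297/3 = 99 low. Other shares give other totals for 198 patients: 425 questionnaires at h = 20%, 372 at 30%, 330 at 40%.

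**2. Reproducing 198.** A one-sample test of 0.90 against a null of 0.70 (not stated, back-solved) needs 42 cases. Then 42/0.25 = 168 and 168/0.85 = 197.6, rounded up to 198. The calculation thus fits the Primary Care prevalence, not that of the enriched sample.

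**3. Composition.** At h = 0.25 the studied sample is 99/198 = 50% Berlin-high, against 25% in the source population. At h = 20%, 30% and 40% it is 43%, 56% and 67%.

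**4. Berlin accuracy.** Assume OSA in 50% of Berlin-high and 25% overall. Then OSA in Berlin-low = (0.25 − 0.25 × 0.50)/0.75 = 16.7%.

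| | High, OSA | Low, OSA | High, no OSA | Low, no OSA |
|---|---|---|---|---|
| Screened (396) | 49.5 | 49.5 | 49.5 | 247.5 |
| Studied (198) | 49.5 | 16.5 | 49.5 | 82.5 |

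- Sensitivity: true 49.5/99 = 50%; crude 49.5/66 = 75%.
- Specificity: true 247.5/297 = 83.3%; crude 82.5/132 = 62.5%.
- In general, with true sensitivity s, crude sensitivity is 3s/(1 + 2s). Here s equals P(OSA | high), because h equals the overall prevalence. For P(OSA | high) from 25% to 60%, the overstatement is 22 to 27 points.
- Missed cases per 100 with OSA: 25 crude, 50 true. This kind of figure would enter the cost analysis.

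**5. AMS alone.** With the same sensitivity in both strata, nothing changes. With assumed stratum sensitivities of 95% (high) and 80% (low):

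- crude: 0.75 × 0.95 + 0.25 × 0.80 = 91%;
- true: 0.50 × 0.95 + 0.50 × 0.80 = 87.5%.

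These lie on either side of the planned 90%.

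**6. AUC.** Over several stratum prevalences, the crude AUC differs from the population value by about 0.001 to 0.003 for AMS and Berlin combined, and by about 0.01 to 0.02 for Berlin alone.

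**7. Price of weighting.** Effective number = (Σw)²/Σw².

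- All 198: (99 × 1 + 99 × 3)²/(99 × 1 + 99 × 9) = 396²/990 = 158.4; design effect 198/158.4 = 1.25.
- Cases among about 168 evaluable (84 high, 84 low; 42 + 14 = 56 cases): (42 + 42)²/(42 + 126) = 84²/168 = 42; design effect 56/42 = 1.33.

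**The case against.** A reader might infer that the protocol prescribes unweighted analyses throughout and that prevalence, predictive values and AUC will all be wrong. The text does not support that.

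- It never calls an analysis unweighted; it is silent. A statistical analysis plan is not at hand and could add weights.
- Prevalence and predictive values are not named as planned outputs.
- The AUC, the stated main objective, hardly moves.
- AMS-alone accuracy is unbiased if it is equal across Berlin strata given OSA status. Logistic coefficients stay valid if the Berlin result is in a correctly specified model.
- No rule requiring Berlin-positive and then AMS-positive is defined, although the Rationale calls the model sequential. Figures for such a gate would be the reviewer's construction.

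A reader might also want to weight for participation, because Limitations warns that "patients accepting their inclusion in the study could be those with greater comorbidity". The 40% acceptance rate there comes from a previous study, and nothing says that decliners' data are kept. At 40% acceptance, 396 questionnaires could give at most 396 × 0.40 = 158 patients. So either 396 is counted after acceptance or the 25% Berlin-high share does not hold.

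All of these points stand, and they narrow the finding. They do not remove it. The protocol fixes the unequal fractions, describes selection elsewhere without them, and sets out an analysis that ignores them. Run as written, that analysis misstates marginal accuracy for any rule using Berlin, and the cost inputs that follow from it.

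**Conclusion.** The point holds in limited form. Sampling depends on the Berlin result with known fractions, the target is Primary Care, and the analyses listed do not allow for it. For Berlin, or a rule that uses it, the distortion can be large: 75% against 50% in sensitivity and 62.5% against 83.3% in specificity in the illustration. For AMS alone it is conditional on accuracy differing by stratum (91% against 87.5% in the example), and for AUC it is small.

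The sizes rest on a 25% Berlin-high share, which requires that every selected patient takes part, and on assumed stratum prevalences and accuracies. None of these is a document figure. The direction for Berlin sensitivity and specificity does not depend on the exact values: whenever low-probability patients are sampled less, crude sensitivity rises and crude specificity falls.

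**What to change.** - In Data management and analysis, state that marginal accuracy and cost results are weighted by the inverse realised sampling fraction (planned 1 for Berlin-high, 3 for Berlin-low). The alternative is to report them by Berlin stratum and standardise to the screened mix. Use design-based or stratified-bootstrap intervals.
- Keep the Berlin result in the logistic model, or fit the model with the weights.
- Keep Berlin results and denominators for all screened patients. This must be in place from the start of screening, because lost denominators may not be recoverable later.
- Reconcile the selection wording in Study population and in Design and Validation Time with Sample size. Say whether the randomization schedule is the 1-in-3 draw.

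The cost is some wording, a screening log and somewhat wider intervals: a design effect of about 1.25 overall and about 1.33 among cases in the example. There, 56 observed cases carry the information of about 42, the number the stated figures imply (198 × 0.85 × 0.25 = 42). If OSA prevalence among Berlin-high patients is 25% to 60%, the effective number of cases is 34 to 47.

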### Methodology

#### 1.- Training Time:

- Leader identification at each center: Primary Care nurses and physicians.
- Training Protocol, in charge of Sleep Units:

Theoretical Training: Four hours of theoretical training for the leaders participating in the project:

- Definition and epidemiology of OSA
- Symptoms and management
- Clinical impact of the disease
- Treatment and prevention
- Assistance aspects

